##### Pathological Diagnostic Standard (Centralized Blinded Assessment)

Pathological Diagnostic Standard evaluates 6 histological changes using a 4-point scale (0: none; +: mild, ++: moderate; +++: severe) via a visual analog scale.

##### Chronic Inflammation (Mononuclear Cell Infiltration)

Chronic inflammation was assessed according to the density and depth of mononuclear cell infiltration. Activity was evaluated based on neutrophil infiltration.

##### Atrophy (Reduction of Intrinsic Glands)

Atrophy was defined as the reduction of gastric intrinsic glands. Scores were classified as 0 (no reduction), + (reduction ≤1/3 of original glands), ++ (reduction >1/3 but ≤2/3 of original glands), and +++ (reduction >2/3 of original glands).

##### IM Grading

Scores were classified as 0 (absent), + (IM area ≤1/3 of gland/surface area), ++ (IM area >1/3 but ≤2/3), and +++ (IM area >2/3).

##### Dysplasia Grading

Dysplasia was graded as + (mild), ++ (moderate), and +++ (severe).

##### Endoscopic Biopsy Protocol (The Updated Sydney System)

Five biopsy specimens were obtained: 2 from antrum (3 cm from pylorus: 6 o'clock greater curve, 12 o'clock lesser curve), 2 from body (8 cm from cardia: 6 o'clock greater curve/mid-body; 4 cm proximal to angle: lesser curve), 1 from the angle. Additional biopsies from any visible lesions.

##### H Pylori Diagnosis

H pylori infection was considered positive based on either biopsy histology or special staining (eg, silver stain), 13C or 14C urea breath test, or a rapid urease test. Proton pump inhibitor, histamine H2 receptor antagonist, bismuth, and antibiotics had to be stopped at least 2 weeks before testing.

#### Participant Selection and Study Discontinuation Criteria

Eligibility criteria, participant withdrawal and dropout criteria, and conditions for trial suspension are summarized in Textboxes 1 and 2.

Participant eligibility criteria.
**Inclusion criteria**
A history of H pylori infection with successful eradication confirmed at least 1 year prior to enrollment.Meet the above diagnostic criteria for chronic atrophic gastritis (CAG) at the time of eradication.Endoscopic and histopathological confirmation of gastric atrophy (reduction of intrinsic glands) with or without intestinal metaplasia, but without dysplasia, prior to enrollment.Age between 35 and 70 years, and gender is not limited.The participant is informed and voluntarily signs the informed consent form.Resident in the local area, able to ensure treatment follow-up, and possesses basic reading comprehension skills.Those who have not taken anticoagulants such as aspirin, warfarin, and those with no coagulation dysfunction.
**Exclusion criteria**
Autoimmune gastritis (type A CAG).Patients with gastric and duodenal ulcers and upper gastrointestinal bleeding.Patients with high-grade intraepithelial neoplasia of the gastric mucosa or suspected malignant transformation by pathological diagnosis.Patients with serious primary diseases such as the heart, brain, liver, kidney, hematopoietic system, and respiratory system.Individuals presenting with comorbid conditions or psychiatric disorders that may compromise treatment assessment or study adherence, as determined by investigators, will be excluded.Female participants who are currently pregnant, breastfeeding, or planning conception within the study period will be excluded.Those with allergies or a history of allergies to multiple drugs (more than 2 or known drugs or ingredients in the study); Allergic to components of the product.Other circumstances that the investigator considers inappropriate for inclusion.Patients who are participating in clinical trials of other medicines.

Participant discontinuation and trial suspension criteria.
**Dropout criteria**
Participants who demonstrate unwillingness or inability to continue trial participation, regardless of the underlying cause, are discontinued.Participants who discontinue therapeutic interventions and protocol-specified assessments without formal withdrawal notification are categorized as passive discontinuations.Cases that have been enrolled but have not completed the clinical protocol are considered to have dropped out if they have the above conditions. The specific reasons for participant dropout are rigorously documented.
**Voluntary withdrawal of participants**
Participants become unwilling or unable to continue trial participation for any reason.Participants become lost to follow-up, meaning they discontinue treatment and study visits without formally withdrawing.
**Conditions for suspension**
The occurrence of any serious adverse event during the treatment period.The identification of a major flaw in the clinical trial protocol that compromises the accurate evaluation of treatment efficacy.Any significant protocol deviation that occurs, if sustained, would compromise the validity of the treatment efficacy evaluation.The principal investigator deems it necessary to discontinue the study.A request to suspend the trial is issued by the drug regulatory authority.

### Sample Size Calculation

The superiority test of the outcome measure Operative Link on Gastritis Assessment (OLGA) improvement rate was used as a categorical variable, and the sample size of the control group was estimated by n1. n2 represents the sample size of the control group, k represents the ratio of the number of cases between the 2 groups (k=1), and the minimum clinically meaningful difference is set △=10%. According to the results of the team’s previous research, π1=45%, π2=10% [12]. By further incorporating a 2-sided significance level (α) of 0.05 and a statistical power of 80%, the calculation yielded n2=43 and n1=43. Considering the 20% clinical dropout rate, the sample size was determined to be 108 cases, that is, 54 cases in the experimental group and 54 cases in the control group.

For the superiority test of categorical variables with the improvement rate of the outcome measure Operative Link on Gastric Intestinal Metaplasia Assessment (OLGIM), in which △=10%, k=1, π1=42%, and π2=8% [12], using the same significance level (α=0.05) and statistical power (80%), the calculation yielded n2=44 and n1=44. Considering the 20% clinical dropout rate, the sample size was determined to be 110 cases, that is, 55 cases in the experimental group and 55 cases in the control group.

The larger calculated sample size was chosen to ensure adequate statistical power. Therefore, the sample size was 110 cases, 55 cases in the experimental group, and 55 cases in the control group.

[figure not shown]

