### Statistical Analysis Plan

The approach of this study is to use an intention-to-treat analysis, ensuring that all participants are included in the analysis as originally assigned. Specialized statisticians will handle the statistical analysis in a blinded manner to maintain the integrity of the results. Regarding missing data, particularly for the primary histopathological end point, we will address this issue using the Last Observation Carried Forward method to impute missing data. This approach will help mitigate the potential bias introduced by incomplete data and ensure that the analysis remains robust. Using SAS software (version 6.12; SAS Institute Inc.), all statistical tests will be 2-sided, with a *P* value of ≤.05 considered to indicate statistical significance. Initially, we will assess the baseline balance to determine the comparability of the intervention and control groups in terms of their fundamental characteristics. For quantitative data, we will provide a comprehensive description including the count, mean, SD, median, and range (minimum-maximum), and use either a *t* test or a Wilcoxon rank sum test to compare the 2 groups. Qualitative data will be presented in terms of frequency and percentage, with a chi-square test or Fisher exact test used to evaluate differences between the groups. In the analysis of combined medication use, we will enumerate the number and percentage of occurrences and then apply a chi-square test or Fisher exact test to analyze any disparities between the groups. For the assessment of treatment compliance, we will enumerate the cases where the administered dosage of the experimental drug falls below 80%, exceeds 120%, or lies within the 80%-120% range and subsequently perform a chi-square test or Fisher exact test to identify any significant differences.

Regarding safety analysis, we will detail the incidence of AEs and serious AEs that occur during the treatment period. We will also present detailed tables outlining the specifics of AEs and serious AEs to provide a thorough understanding of the safety profile of the treatment.

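### The sample size is built on superiority by more than 10 points, but the stated test is of zero difference, so the stated 80% is not that test's power

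*Protocol article*

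**What the plan says.** The Sample Size Calculation section of the protocol article bases the size on a superiority comparison: "The superiority test of the outcome measure Operative Link on Gastritis Assessment (OLGA) improvement rate was used as a categorical variable". It then says that "the minimum clinically meaningful difference is set △=10" percent. The planning rates are 45% versus 10% for OLGA. For OLGIM the inputs are given as "in which △=10%, k=1, π1=42%, and π2=8" percent. Both calculations use a "2-sided significance level (α) of 0.05 and a statistical power of 80" percent. For OLGA, "the calculation yielded n2=43 and n1=43"; for OLGIM, "the calculation yielded n2=44 and n1=44". After a 20% dropout allowance these become 54 and 55 per arm, and the larger total of 110 is adopted.

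The Statistical Analysis Plan section of the same article makes all tests two-sided at the 5% level and handles qualitative data by frequency and percentage, "with a chi-square test or Fisher exact test used to evaluate differences between the groups". It specifies intention-to-treat analysis, with last observation carried forward for missing primary histology. The 10 points do not reappear there, or anywhere else, as a hypothesis, a test or a confidence-limit criterion.

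**The concern.** If the 10 points act as a margin in the sizing, the null hypothesis behind N=110 is that the difference in regression rate is at most 10 points. A chi-square or Fisher test has a different null, a difference of zero. The power statement then describes one test and the analysis section another.

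What is at stake is interpretation. The protocol names 10 points as the smallest difference it regards as clinically meaningful and uses it to justify N. A reader of the final report could take a significant P value as meeting that standard, although the stated test needs a much smaller observed difference. If the role of the 10 points stays open, it may be settled only after the data are seen.

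**Working it through.** **Inputs** (all from Sample Size Calculation): π1/π2 = 0.45/0.10 (OLGA) and 0.42/0.08 (OLGIM); Δ = 0.10; two-sided α = 0.05; power 80%; 1:1 allocation; dropout 20%. (1.960 + 0.842)² = 7.849. The formula figure is not shown, so the formula is identified by reproducing the results.

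**1. Reproducing the stated n, with Δ as a margin**

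n = [π1(1−π1) + π2(1−π2)] × 7.849 / (π1 − π2 − Δ)²

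- OLGA: (0.2475 + 0.0900) × 7.849 / 0.25² = 42.38, rounded up to 43. 43/0.8 = 53.75, so 54.
- OLGIM: (0.2436 + 0.0736) × 7.849 / 0.24² = 43.22, rounded up to 44. 44/0.8 = 55.

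All four stated figures match.

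**2. Same inputs, no margin**

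- Unpooled variance: 0.3375 × 7.849 / 0.35² = 21.6 and 0.3172 × 7.849 / 0.34² = 21.5, so 22 per arm for each.
- Usual formula with pooled variance under the null: 25 and 25.
- With continuity correction: 30 and 30.

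None gives 43 or 44. A 10-point margin at one-sided 0.05 gives 34 and 35, which also fails to match. So Δ entered as a superiority margin at two-sided 0.05.

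**3. Power at the planning rates, by exact binomial enumeration**

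| Test | OLGA, 44 per arm | OLGIM, 44 per arm |
|---|---|---|
| Chi-square, difference = 0 | 97.5% | 97.8% |
| Fisher exact, difference = 0 | 95.2% | 95.5% |
| Wald test, difference ≤ 10 points | 81.6% | 81.5% |
| Farrington-Manning, difference ≤ 10 points | 79.9% | 79.9% |

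The 80% belongs to the margin test.

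**4. What a significant result would show (55 per arm, 5 placebo regressions)**

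- Chi-square first reaches 5% at 13 versus 5: difference 8/55 = 14.5 points, Wald 95% CI 1.0 to 28.1.
- The lower 95% limit first exceeds 10 points at 19 versus 5: difference 14/55 = 25.5 points.
- From 13 to 18 regressions on WW-1, the stated test is significant while 10 points are not excluded.

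**5. Effect of the protocol's own missing-data rule**

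Table 1 schedules gastroscopy and pathology only at visits 1 and 8. A participant without visit 8 therefore has baseline carried forward and counts as not regressed. Assume 20% dropout, equal by arm, with the planning rates holding in completers:

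- OLGA: 0.8 × 45% = 36% versus 0.8 × 10% = 8%.
- OLGIM: 0.8 × 42% = 33.6% versus 0.8 × 8% = 6.4%.

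Exact power at 55 per arm is then about 96% to 97% for chi-square against zero, but about 67% for the margin test by Miettinen-Nurminen (68% by Wald).

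**The case against.** The strongest reply is that the mismatch is conservative. The stated test has more power than claimed, the chi-square test is a valid test of zero difference, and in a placebo-controlled trial rejecting zero is properly called superiority. The article's stated hypothesis is that WW-1 improves histology, which a test against zero answers. All of this stands.

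A reader might go further and infer that the trial will declare superiority by more than 10 points on the strength of a chi-square P value. The document does not support that. It gives no explicit success criterion, and it presents the 10 points as a clinically meaningful difference, not as a null hypothesis. For the same reason, the chance of about 31% that chi-square is significant when the true rates are 20% versus 10% (55 per arm) is not a false-positive rate. It is ordinary power against a real benefit of 10 points.

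It can also be said that the chi-square or Fisher sentence covers qualitative data in general without naming the primary endpoint, and that a separate analysis plan may carry the margin. Both are fair limits. They do not remove the mismatch. The sample-size section treats OLGA improvement as categorical, and the article states one kind of between-group test for such data, whose null differs from the one behind N. If the 10 points were meant only as description, subtracting them in the calculation was wrong for the stated test.

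**Conclusion.** The point holds as an inconsistency between sizing and analysis; should-fix. N=110 was derived for superiority by more than 10 points, and the stated test addresses zero difference. Its power at the planning rates is about 97% to 98% (chi-square, 44 evaluable per arm), not 80%. Nothing is lost in power or validity for the stated test. What is lost is a clear meaning for the 10 points: in the worked example, the two thresholds lie 6 responders apart out of 55.

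The margin reading rests on the superiority wording and on exact reproduction of both stated sample sizes, because the formula itself is not shown. The power figures assume that the planning rates are true. The 67% further assumes 20% dropout, equal by arm, with carried-forward cases counted as not regressed.

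**What to change.** Settle the role of the 10 points before unblinding, by one of two routes.

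**(a) Test against zero only.** Keep the chi-square or Fisher test, delete the margin from the sample-size justification, and restate the power as about 97% with 44 evaluable per arm (chi-square). Add that it is about 96% to 97% at 55 per arm if 20% are carried forward as not regressed.

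**(b) Keep the margin as a second claim.** Report the difference in regression rate with a two-sided 95% CI. Test zero first; only if that succeeds, claim superiority by a clinically meaningful amount when the lower limit exceeds 10 points. The fixed order spends no extra alpha. State that this second claim has about 80% power with 44 complete per arm at the planning rates, but only about 67% at 55 per arm under intention-to-treat with last observation carried forward and 20% dropout.

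Either route changes wording in the sample-size and analysis sections and leaves N at 110. The cost of (b) is a higher bar and a less favourable stated power for the margin claim; the cost of (a) is that a significant result carries no claim about the 10 points.

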### Randomization, Allocation, and Blinding

In this study, case collection is being carried out in 4 institutions (Wangjing Hospital of China Academy of Chinese Medical Sciences, Shanxi Provincial Hospital of Traditional Chinese Medicine, Second Affiliated Hospital of Baotou Medical College, and Hubei Provincial Hospital of Traditional Chinese Medicine). The study uses a stratified block randomization method. Stratification is based on both the research center and the baseline OLGA/OLGIM stage. The third-party statistical agency used SAS software (SAS Institute Inc) to generate a random number list, and each clinical research center randomly allocates the qualified participants to the experimental group and the control group according to the ratio of 1:1. The trial is also designed as a double-blind trial. The blinding is conducted by independent personnel, and the blind record is formed. To ensure the integrity of the blinding, all medications and placebos are uniformly packaged. According to the Standard for the Use of Food Additives in the National Standard for Food Safety, the placebos are prepared from starch, dextrin, food coloring, bitters, etc, based on the type and volume of the raw materials. In appearance, color, dosage form, quality, taste, and odor, it is the same as or basically similar to the experimental drug, but does not contain the active ingredient of the experimental medicine.

All randomization code envelopes must remain strictly sealed, with any unblinding requiring full documentation of personnel, date/time, and rationale, immediately recorded in the case report form (CRF). Emergency unblinding is only permitted for life-threatening situations requiring knowledge of the investigational product, and must involve joint authorization by the clinician and study director, followed by participant discontinuation and detailed CRF documentation. Post study, all unsealed envelopes undergo verification and final blinded review by an independent audit team to ensure compliance with International Council for Harmonisation of Technical Requirements for Pharmaceuticals for Human Use-Good Clinical Practice and regulatory standards.

### Intervention Method

#### Overview

All participants receive standardized patient education and consultation regarding lifestyle, diet, and disease management throughout the study period.

On this basis, participants in the intervention arm receive active WW-1 granules, whereas the control arm receives visually identical placebo preparations. Both formulations were produced by Hunan Xinhui Pharmaceutical Co., Ltd. (Hunan, China) and authenticated using HPLC-MS analysis. The matched placebo replicates the active drug in all sensory characteristics (color, aroma, and flavor) and packaging. To maintain strict blinding integrity against the distinct sensory characteristics of the herbal formula, the placebo granules were formulated with a subtherapeutic dose (5%) of the WW-1, combined with matching pharmaceutical excipients. This 5% concentration aligns with the technical guidelines for TCM clinical trials issued by the National Medical Products Administration of China, providing necessary sensory fidelity without exerting any pharmacological therapeutic effect.

Both groups follow an identical administration regimen: oral intake of 1 sachet twice daily for 24 weeks. No additional pharmacological treatments for CAG are permitted during the trial. The overall timeline of this double-blind study, including treatment allocation and evaluation points, is presented in Table 1.

**Table 1 table1:** Schedule of the multicenter, randomized, double-blind, placebo-controlled clinical trial.

Stage procedure	Screening period	Washout period	Treatment period						
	Visit 1 (–14 d ~ 0 d)	1 week	Visit 2 (0 day)	Visit 3 (4 weeks)	Visit 4 (8 weeks)	Visit 5 (12 weeks)	Visit 6 (16 weeks)	Visit 7 (20 weeks)	Visit 8 (24 weeks)
Screening for inclusion/exclusion	✔								
Sign informed consent form	✔								
Demographic data	✔								
Disease risk factors	✔								
Past medical history	✔								
Medical comorbidities and current medication	✔			✔	✔	✔	✔	✔	✔
C13/C14 urea breath test	✔								
Gastroscopy and pathology	✔								✔
Tongue coating, saliva, stomach and fecal microbiota collection	✔								✔
TCM^a^ syndrome scoring			✔	✔	✔	✔	✔	✔	✔
Vital signs	✔		✔	✔	✔	✔	✔	✔	✔
Blood routine	✔								✔
Urine routine	✔								✔
Stool routine and occult blood	✔								✔
Liver function tests (AST^b^ and ALT^c^)	✔								✔
Renal function tests (BUN^d^ and Cr^e^)	✔								✔
Electrocardiogram	✔								✔
Adverse events				✔	✔	✔	✔	✔	✔
Dispensing medication			✔	✔	✔	✔	✔	✔	
Combination therapy medication record			✔	✔	✔	✔	✔	✔	✔
Drug return and record				✔	✔	✔	✔	✔	✔
Trial summary									

^a^TCM: traditional Chinese medicine.

^b^AST: aspartate aminotransferase.

^c^ALT: Alanine aminotransferase.

^d^BUN: blood urea nitrogen.

^e^Cr: creatinine.

#### Drug Interaction Management Principles

During the trial, Chinese medicines and proprietary Chinese medicines with similar efficacy in the treatment of CAG or similar effects cannot be used. Gastric mucosal protectants and/or proton pump inhibitors can be used for a short period of time once a month for less than 7 days, and are recorded in detail on a CRF. If the participant has comorbid diseases and must continue to maintain these medications or treatments, the disease, the name of the medication, the dose used, the frequency of use, the route of administration, and the start and end times must be recorded in detail. Any changes in the participant’s medication throughout the study are also recorded in detail on the CRF for analysis and reporting at the time of summary. At each follow-up visit, the researchers keep a detailed record of whether the participants took their medications on time and count the number of medications returned. Keep a record of lost or unreturned medications. If the participant’s compliance is not good, the cause should be found and documented. The investigator should record the number of drugs issued and returned in the corresponding section of the CRF. Patient compliance is calculated as the percentage of the actual total medication taken relative to the total medication required by the study protocol, using the formula: (actual total medication taken/total protocol-required medication) × 100%.

### Outcome Evaluation

The primary outcome, OLGA improvement, is evaluated based on assessments at baseline (visit 1) and posttreatment (visit 8). The severity of gastric atrophy is assessed at baseline and post-treatment according to the OLGA staging system, with the overall stage at each time point determined by the most severe atrophic grade across all biopsy sites. Patients are categorized into three groups based on changes in OLGA stage: regression, defined as a reduction of ≥1 stage after treatment; stable, defined as no change in OLGA stage after treatment; and progression, defined as an increase of ≥1 stage after treatment.

Secondary outcomes include the improvement of gastric mucosal atrophy and IM (assessed at visits 1 and 8), as well as changes in TCM syndrome scores (assessed at visits 1, 2, 3, 4, 5, 6, 7, and 8). Based on the histopathological characteristics of CAG, a graded scoring system will be used for the pathological assessment. The severity of gastric mucosal atrophy and IM will be classified into 4 grades—absent, mild, moderate, and severe—which will be assigned scores of 0, 2, 4, and 6, respectively. In cases where multiple biopsy specimens or histological sections from a single patient exhibit varying degrees of lesions, the score corresponding to the most severe lesion will be assigned. The improvement in these pathological scores from baseline to posttreatment will be compared between the 2 groups. Additionally, clinical symptoms will be quantitatively evaluated using a standardized scoring method. The primary symptoms include stomach pain and fullness, while secondary symptoms encompass gastric discomfort, poor appetite, dry mouth, bitter taste in the mouth, belching, acid reflux, heartburn, and fatigue. The symptom grading criteria are formulated according to the *Guiding Principles for Clinical Research of New Traditional Chinese Medicines* (2002 edition). Specifically, primary symptoms will be comprehensively assessed based on their severity and frequency, and categorized into 4 grades (absent, mild, moderate, and severe), scoring 0, 2, 4, and 6 points, respectively. Secondary symptoms will be evaluated using the same 4-tier scale but will be scored as 0, 1, 2, and 3 points, respectively. The total symptom scores will be recorded at baseline and at 4-week intervals throughout the treatment period. Changes in the total symptom scores relative to baseline will be compared between the 2 groups to comprehensively assess symptom improvement.

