### Comparison to Prior Work

Currently, the internationally recognized approach to intervening in the cancer transformation process of CAG primarily focuses on eradicating *H pylori*. However, research has demonstrated that, among individuals infected with *H pylori*, the number of patients with gastric atrophy continues to significantly increase even 1 year after eradication therapy [20]. In comparing changes in gastric mucosal lesions before and after eradication therapy, scholars often regard IM as a “point of no return” in the cascade model of GC. For instance, a meta-analysis involving 12 studies and 2658 patients revealed that eradicating *H pylori* significantly improved atrophy in the gastric body but did not alleviate atrophy or IM in the gastric antrum. A Japanese study found that gastric body IM, regardless of extent, was an independent predictor of GC development after *H pylori* eradication [22]. A long-term randomized controlled trial following 800 patients with CAG in a region of Colombia with high GC incidence for 20 years found that gastric mucosal lesion scores began to decline only 3 years after achieving *H pylori* negativity [6]. Therefore, delaying the inflammation-carcinoma transformation induced by *H pylori* represents a critical and challenging step in the prevention of GC. Actively and effectively conducting intervention studies targeting this transformation process is of great significance for GC prevention and control. Currently, there is a lack of specific therapeutic agents supported by high-quality evidence-based medicine. Existing treatment strategies are mainly focused on symptom relief and regular endoscopic and histopathological surveillance, with limited clinical efficacy. TCM, based on a holistic perspective, demonstrates multidimensional advantages in managing gastric precancerous lesions. Our previous multicenter trial, conducted in collaboration with [name] team, indicated that a 24-week intervention with WW-1 significantly improved atrophy scores in the gastric body and angle compared to placebo [12]. Given its proven efficacy in reversing general gastric atrophy, we postulate that WW-1 holds substantial therapeutic potential for the treatment of CAG following *H pylori* eradication.

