The digestive tract microbiota has a significant influence on epigenetic modifications, including DNA methylation in the host, which plays a key role in the development of multiple diseases. Intestinal microbiota can modulate gut homeostasis and inflammation by regulating DNA methylation [26]. Our study will provide novel insights into the potential correlation between digestive tract microbiota and DNA methylation and elucidate the specific regulatory mechanisms underlying CAG and precancerous lesions for the first time.

The collection of digestive tract microbiota strictly adheres to established protocols. Our team possesses extensive research expertise in the field of microbiota, ensuring the implementation of standardized procedures and establishing a solid foundation for obtaining high-quality data [14,27]. Simultaneously, our standardized gastric mucosal sample collection and rigorous double-blind pathological evaluation of the gastric mucosa are pivotal for assessing WW-1 efficacy and lay the foundation for further elucidating the mechanism of WW-1. Accurate and adequate gastric mucosal biopsies are essential for determining the extent of gastric mucosal lesions and for risk stratification of GC using the OLGA and OLGIM staging systems. According to the updated Sydney system gastritis classification method [28], our study takes 5 biopsies from the gastroscope, including 2 from the antrum, 2 from the body, and 1 from the angle of the stomach, so that the efficacy of TCM can be observed overall and in different parts. The mucosa of the antrum minor, the site selected for the collection of the gastric flora under endoscopy, also meets the collection standards certified by high-quality research [29].

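### The primary OLGA stage is set by the single worst atrophy grade at any biopsy site, so it ignores extent and location and rests on the same measure as the secondary atrophy score

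*Protocol article*

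**What the plan says.** All references are to the protocol article.

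- **Primary outcome (Outcome Evaluation).** Atrophy is assessed at visits 1 and 8 under the OLGA system, "with the overall stage at each time point determined by the most severe atrophic grade across all biopsy sites". Response is "regression, defined as a reduction of ≥1 stage after treatment"; the other categories are stable and progression.
- **Secondary atrophy and metaplasia scores (same section).** Severity "will be classified into 4 grades—absent, mild, moderate, and severe—which will be assigned scores of 0, 2, 4, and 6, respectively". Where specimens differ, "the score corresponding to the most severe lesion will be assigned".
- **Biopsies (Endoscopic Biopsy Protocol).** Five specimens are taken: two antrum, two body, one angle. The section then adds: "Additional biopsies from any visible lesions".
- **Purpose of the biopsies (Discussion, Comparison to Prior Work).** They are described as needed to determine lesion extent and to stratify cancer risk by OLGA and OLGIM. Five sites are sampled "so that the efficacy of TCM can be observed overall and in different parts".
- **Earlier evidence (same section).** The previous trial of WW-1 "significantly improved atrophy scores in the gastric body and angle compared to placebo".
- **Other uses of the stage.** Sample Size Calculation plans on OLGA improvement of 45% vs 10% and OLGIM improvement of 42% vs 8%. Randomization is stratified by center and baseline OLGA/OLGIM stage.

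**The concern.** A maximum over sites records how bad the worst specimen is. It does not record how much of the stomach is affected or which part. The article wants OLGA for extent and wants to see efficacy by region, so the stated rule conflicts with the stated purpose.

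Three things are at stake:

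1. The primary result would be reported as an OLGA result without measuring what the article says OLGA is for.
2. The rule can miss benefit, including benefit in the body and angle where the earlier trial found it, and it can count spread as success.
3. The secondary atrophy outcome takes the same worst grade, so agreement between it and the primary would add little.

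**Working it through.** **Step 1. The plan's own figures.** The sample size arithmetic is sound. With a margin of 0.10, two-sided alpha 0.05, 80% power and unpooled variance:

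n per arm = (1.960 + 0.842)² × [p1(1−p1) + p2(1−p2)] / (p1 − p2 − 0.10)²

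- OLGA (0.45 vs 0.10): 7.849 × 0.3375 / 0.25² = 42.38, so 43; 43/0.8 rounds up to 54 per arm, 108 in total.
- OLGIM (0.42 vs 0.08): 7.849 × 0.3172 / 0.24² = 43.22, so 44; 44/0.8 = 55 per arm, 110 in total.

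Both match the article. The issue is what the endpoint measures.

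**Step 2. The rule applied.** Each specimen has an atrophy grade from 0 to 3 (section on atrophy grading). Order the five sites as antrum, antrum, angle, body, body. Under the stated rule, stage = max(grades).

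| Before | After | Stage | Sum of grades | Classified as |
|---|---|---|---|---|
| 3,3,3,3,3 | 3,0,0,0,0 | 3 → 3 | 15 → 3 | stable |
| 3,2,2,2,2 | 3,0,0,0,0 | 3 → 3 | 11 → 3 | stable |
| 3,0,0,0,0 | 2,2,2,2,2 | 3 → 2 | 3 → 10 | regression |

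In the first two rows the angle and both body sites clear completely, and the primary endpoint does not move because one antral site keeps the worst grade. In the third row the affected sites go from one to five and the patient counts as improved.

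**Step 3. How often one site's improvement registers.** A one-grade improvement at one site lowers the maximum only if that site alone holds the worst grade.

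- Possible single-site improvements over all five-site patterns: 5 × 3 × 4⁴ = 3,840.
- Those that lower the maximum: 5 × (1⁴ + 2⁴ + 3⁴) = 5 × 98 = 490.
- Share: 490/3,840 = 12.8%.

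This weights all patterns equally. It shows how the rule behaves and does not estimate what happens in patients.

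**Step 4. Overlap with the secondary.** The secondary atrophy score is 0, 2, 4 or 6 for worst grade 0, 1, 2 or 3, so score = 2 × stage. There are 4⁵ = 1,024 five-site patterns and 1,024² = 1,048,576 before/after pairs. A fall in stage and a fall in score disagree in none of them.

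**Step 5. Other rules in the article.** No section shown gives a different way of combining antrum, angle and body grades into a stage.

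**The case against.** **A benign reading exists.** The sentence invokes the OLGA system first, and the clause on the worst grade may compress a rule in which the worst grade within each region feeds that system. This is a journal article and the full protocol is not shown. That stands as a possible intention, but the text takes the maximum across all sites. It is a stated rule, not a detail left out, and needs correcting on either reading.

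**The staging grid is not printed.** This is true. The finding therefore rests on the conflict between Outcome Evaluation and the Discussion, not on an outside account of OLGA.

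**A reader might infer that the two atrophy endpoints are the same variable.** That goes too far. The primary keeps only the direction of change, whereas a score comparison keeps its size: severe to absent is 6 points and severe to mild is 4, yet both are regression. The secondary also covers metaplasia. What stands is that the underlying atrophy measure is the same and the direction always agrees.

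**A reader might infer that power collapses.** The documents do not support this. The 45% and 10% are patient-level rates. Treating them as independent per-site rates has no basis, and if the earlier trial used the same worst-grade rule, nothing is lost. Any power figure would also depend on whether the test uses the 10-point margin of the sample size section or the plain chi-square or Fisher test of the analysis section.

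**A reader might infer that lesion-directed biopsies make the maximum run over different numbers of specimens at the two visits.** The article does not say they enter the stage. Listing five biopsies for staging suggests they may not. This is an ambiguity to close, not a shown error.

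**Conclusion.** The primary endpoint is wrong as written. A maximum of site grades cannot show extent or location. It misses improvement at any site that does not hold the worst grade, and at some but not all sites that share it. It can also record spread as regression. For atrophy, the secondary score is twice the primary stage and is not independent support; the metaplasia part is unaffected.

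These conclusions follow from the stated rule and need no assumption about patients. How many participants would be misclassified, and what the rule does to power, cannot be determined from the article: it gives neither the distribution of site grades nor the rule behind the planning rates. The rule applies equally to both arms and is read blind, so the concern is what the endpoint means and what it can detect; it does not show bias toward either arm.

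**What to change.** 1. Replace the sentence in Outcome Evaluation. Derive the OLGA stage, and likewise the OLGIM stage, by combining the antrum/angle and body grades under the named staging system, and write the combination rule out in full.
2. State that only the five protocol biopsies enter the stage, at both visits.
3. Keep the worst-grade score as the secondary outcome only, and do not present its atrophy part as independent confirmation of the primary.
4. Use the same stage definition for the randomization strata. Participants already randomized keep their assigned stratum, with the rule that was used documented.
5. Confirm that the 45%/10% and 42%/8% rates were obtained under this definition. If not, restate the basis of the sample size.

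The cost is a documented amendment, made before unblinding, and a short derivation program. The five biopsies are already in the protocol and are read centrally, so no extra procedure is needed. The one open cost is the sample size, if the planning rates turn out to rest on another rule.
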